## Abstract

**Background:**

Alcohol use disorder and depression occur commonly in the community. Even though this high-prevalence comorbidity is associated with poorer posttreatment outcomes and greater utilization of costly treatment services, existing treatment trials often exclude patients with comorbid depressive and alcohol use disorders. Past research suggests that symptoms such as craving and anhedonia might be associated with alterations within the reward circuit, while emotion regulation deficits are related to disruptions within the default mode network. The aim of this clinical neuroimaging study is to transfer previous research about the reward circuit and default mode network underlying alcohol use disorder and depression to achieve a better understanding of neural signatures characterizing their comorbidity. In addition, the neurobiological results will be used to test whether two psychotherapeutic intervention programs, mindfulness-based training and behavioral activation training, are able to positively influence the identified pathomechanisms.

**Methods:**

By means of functional magnetic resonance imaging (fMRI), 60 comorbid alcohol dependent and depressed patients are compared to 30 patients with depression only, 30 patients with alcohol use disorder only and 30 healthy control participants. Comorbid patients are randomized to either receive a behavioral activation or mindfulness based training and asked to participate in a second fMRI session and 3 month follow-up assessment. Thereby, we plan to explore whether these brief group psychotherapeutic intervention programs are able to positively influence the identified neurobiological pathomechanisms. The primary outcomes are reward and default mode network activity and connectivity evoked by paradigms measuring different facets of reward and emotion processing. Secondary outcome measures include craving and depression scores, as well as relapse rates. Predictors include participants’ characteristics, personality traits and indicators of mental health.

**Discussion:**

The objective of the project is to identify common and/or distinct neural signatures underlying the comorbidity of alcohol dependence and depression. If the neurobiological understanding of alcohol addiction and depression is improved, this could potentially serve as a key predictor of treatment response to specific types of behavioral or mindfulness therapies hypothesized to alter reward and resting state systems.

**Trial registration:**

German Clinical Trial Register DRKS00010249. The trial was registered January 23th 2017.

## Background

The prevalence of affective disorders in alcohol addiction is estimated to be 22.9% [1, 2] and the presence of alcohol dependence increases the risk for depression by a factor of almost 5 (odds ratio = 4.7) [3]. Despite the tremendous implications for prevention, treatment, and disease progression, the mechanisms underlying this comorbidity are not well understood. So far, studies with neuroimaging technologies, such as functional magnetic resonance imaging (fMRI), paired with behavioral measurement paradigms, have identified the brain’s reward system, as well as resting state networks like the default mode network (DMN) to play critical roles in the understanding of both alcohol dependence and depression.

## Target neurobiological mechanisms of alcohol dependence and depression: Reward System

Increasing evidence in humans and animals suggest that depression and alcohol dependence are associated with major disruptions within the reward circuit, which normally serves to guide our attention towards and consumption of natural rewards.

In major depression, several studies consistently report that activity in the nucleus accumbens (NAc), as part of the ventral striatum (VS), is reduced [4–7] reflecting a loss of reward function that drives symptoms such as anhedonia [8, 9]. Moreover, a recent study showed that depressive symptoms correlated with dysfunction in reward anticipation regardless of diagnostic entity [10]. Furthermore, specifically frontostriatal regions during reward processing have been suggested as an important psychophysiological marker of depression [11, 12]. In line with this, depressed individuals showed reduced frontostriatal activity during reward anticipation [5, 9, 13, 14] and outcome [13, 15].

In alcohol dependence, there is considerable evidence that the VS is activated by alcohol- associated cues and is thereby highly responsible for the incentive salience or “wanting” of goal objects such as alcohol [16–19]. However, whether the activation of the mesolimbic reward system results in alcohol consumption depends on the ability of higher-order structures to regulate incentive reward processing. Prevailing theories of addiction point to the involvement of the prefrontal cortex (PFC) not only through its engagement in executive functions, essential for goal-directed behavior (e.g. coding action-outcome conjunctions, salience attribution or self-control), but also through its monitoring of the mesolimbic reward system [20–22]. Past research suggested that aberrant incentive salience to rewards is not solely restricted to alcohol-associated cues, but also to non-dug rewards [23, 24]. These studies showed that alcohol dependent patients show reduced activation of the VS during the anticipation of monetary gain. On the contrary, recent results from our own group provided evidence that alcohol dependence is characterized by an imbalance between increased ventral striatal activation and weakened prefrontal control, as characterized by decreased frontostriatal connectivity during the anticipation of monetary reward [25]. These inconsistent findings might suggest the presence of different subgroups of alcohol dependent patients showing distinct forms of VS reward-regulating dysfunctions. Hence, it is hypothesized that alcohol dependent patients show diverse risk profiles characterizing distinct neural subgroups, which might be associated with comorbidities like depression.

In summary, in depression as well as in alcohol dependence, activity of the VS, as a pivotal node of the reward system, as well as frontostriatal connectivity have been shown to be altered during reward processing, emphasizing the essential importance of the reward system for both disorders.

## Target neurobiological mechanisms of alcohol dependence and depression: Default mode network

Recent efforts to understand the pathophysiology of major depression have focused on resting-state brain networks. There has been increased emphasis lately on conceptualizing depression as a disorder of functional brain connectivity [26] focusing on network interactions among cortical and subcortical regions. Among other identified neural networks, the default mode network (DMN) has received the most attention in the context of the clinical neuroscience of depression and has also sparked research interest in other psychiatric conditions [27]. The DMN is active and synchronized when the brain is “at rest” (i.e. not engaged in externally imposed goal-directed activity) and is compromised of the posterior cingulate cortex, medial prefrontal cortex and the angular gyri. The DMN has repeatedly been associated with rumination [28, 29], a recurrent, self-reflective and uncontrollable focus on depressed mood, which is thought to play a central aspect of the phenomenology of depression [30] and has also been found to be predictive for relapse and drinking status in alcohol dependent patients [31]. In a study from our own group, we could show that increased DMN connectivity in remitted depressed patients is associated with sadder mood, more rumination in daily life, as well as higher rumination and depression scores after six months [32].

A rather recent line of neuroimaging research has focused on resting state network properties in alcohol dependence. However, results are rather inconsistent, reporting either increased DMN connectivity [33] which was found to be related to relapse [34], mixed results of increased and reduced within DMN connectivity [35] or reduced connectivity [36] which was found to be correlated with poorer inhibitory control [37]. These heterogeneous results might implicate the existence of different subgroups or pathological states that modulates resting state connectivity in alcohol dependence. One modulating factor might be depression.

## Neurobiological informed treatment interventions for comorbidity: Psychotherapy

The ultimate goal of a better understanding of the neurobiological underpinnings is to develop preventive and more effective treatment strategies. Compared to antidepressant or anticraving medication, less research has examined functional neural responses after psychotherapy. Available data suggest that psychotherapy predicts metabolic changes in reward, cingulate and frontal cortices in alcohol dependence [38] and depression [39, 40].

To our knowledge, only a few studies evaluated the effects of a specific psychotherapeutic intervention like the brief Behavioral Activation Treatment (BAT) for depression on brain activation. Dichter and colleagues [41] report functional changes in reward associated structures including the dorsal striatum during reward anticipation after a BAT intervention but did not include a depressed control group. Looking on the DMN connectivity, Crowther and colleagues [42] found that the response to BAT in depressed patients was predicted by pretreatment connectivity of the right insula with the right middle temporal gyrus and the left intraparietal sulcus. Another psychotherapeutic intervention with potential effects on resting state networks is mindfulness based therapy (MBT). MBT is a meditation practice that is recently receiving growing attention for its potential clinical applications in the context of alcohol dependence and depression [43]. Neuroimaging studies showed that long-term meditators showed increased activation of prefrontal areas during meditation as compared with a rest condition or with matched control subjects naïve to meditation practice [44, 45].

In summary, dysfunctions in the reward circuit, as well as DMN have been identified as key domains underlying alcohol dependence and depression. We assume that these mechanisms also characterize the neurobiological underpinning of their comorbidity. Thereby, the identification of neural risk factors associated with their co-occurrence might help in understanding the pathophysiological mechanisms leading to their onset and course. The overall goal of improving our understanding of neurobiological mechanisms is to improve treatment. If the neurobiological understanding of alcohol dependence and depression is improved, this could potentially serve as a key predictor of treatment response to specific types of behavioral (BAT) or mindfulness (e.g. MBT) therapies shown to alter reward and resting state systems.

## Aim

The primary aim of this project is to identify neurobiological mechanisms underlying the psychopathology of comorbid alcohol dependence and depression. Subsequently, we plan to explore whether a brief psychotherapeutic intervention program is able to positively influence these pathomechanisms and if we can identify neurobiological signatures at baseline that predict the response to the particular intervention. To facilitate the achievement of the overall project objective, it has been broken down into several sub-objectives which represent a stepwise procedure towards the achievement of the primary aim:Identification of neurobiological mechanisms underlying comorbid alcohol dependence and depressionBy means of comparing comorbid patients with alcohol dependent, depressed and healthy control subjects, we aim to understand distinct and common neuronal signatures and its target mechanisms that cut across both disorders.By identifying specific signatures related to the reward circuit and default mode network we will be able to recognize potential subgroups.
Development and application of psychotherapeutic interventions targeting these mechanismsIf the neurobiological understanding of comorbid alcohol dependence and depression is improved, this could potentially serve as a key predictor of treatment response to specific established behavioral and mindfulness based intervention programs shown to improve clinical symptoms.
Evaluation of intervention on the neurobiological levelBy evaluating the psychotherapeutic interventions on the neurobiological level, we will be able to identify neurobiological markers of therapy efficiency (change of brain signatures after psychotherapeutic intervention).
Prediction of therapy response by means of neurobiological measuresBy predicting psychotherapeutic success by means of neurobiological signatures, we will gain first insights in neurobiological constructs to guide selection of distinct therapy targets and ultimately help to structure the personalization of psychotherapy.

## Methods

### Study design

In this randomized-controlled trial, comorbid alcohol dependent and depressed patients will be compared to depressed only, alcohol dependent only and healthy control participants. All participants are screened and after examination of inclusion and exclusion criteria admitted to the study. All participants will receive a baseline fMRI session (T1). Subsequently, only comorbid alcohol dependent and depressed patients will be randomized to either receiving group BAT or MBT training for 6 weeks. Afterwards comorbid patients will receive an outcome fMRI session (T2) and will be contacted after three months for a catamnestic exploration. For a flow chart of the study design please refer to Fig. 1.

**Fig. 1 Fig1:**
[figure not shown]
Flow Chart of the study design. Abbreviations: AUD = Alcohol use disorder patients, Co = Comorbid alcohol dependent and depressed patients, MD = Major depressive patients, HC = Healthy Controls, fMRI = functional magnetic resonance imaging

### Participants

Sixty comorbid alcohol dependent and depressed patients, 30 alcohol dependent only and 30 depressed only patients will be included for T1 assessment. Further, 30 healthy control participants (matched according to age, gender and educational level) will be recruited.

### Eligibility

All participants will be 1) aged between 18 and 65 years, 2) have to provide informed consent, 3) be right-handed, 4) show an appropriate comprehension of the German language and 5) must be able to accurately watch visual stimuli in the scanner environment. Alcohol use disorder and depression will be diagnosed according to DSM-5 criteria and patients must be abstinent for at least 5 days before scanning. Exclusion criteria for all participants include 1) psychiatric Axis I disorders as measured by the SCID I interview within the past 12-months (except for patients alcohol and nicotine abuse and depressive symptoms), 2) neurological disorders, 3) MRI specific contraindications such as having a pace maker or implanted metal, 4) positive drug screening (opioids, cannabinoids, benzodiazepines, barbiturates, cocaine, amphetamines), 5) any current psychoactive medication except anti-depressants, 6) pregnancy and 7) suicidal tendencies. During the participation in the group therapies, comorbid participants should not enroll in any other CBT or individual psychotherapeutic treatment.

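### The 12-month look-back on Axis I disorders lets people with earlier, remitted depression or alcohol dependence enter as healthy controls, although the protocol treats default mode connectivity as informative in remitted depression

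*Protocol article*

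**What the plan says.** In the protocol article, Eligibility opens its exclusion list for all participants with "psychiatric Axis I disorders as measured by the SCID I interview within the past 12-months". A bracket follows that lifts the exclusion for the disorders under study, but in patients only: "except for patients alcohol and nicotine abuse and depressive symptoms". Group diagnosis is covered by one sentence: "Alcohol use disorder and depression will be diagnosed according to DSM-5 criteria". The medication criterion excludes "any current psychoactive medication except anti-depressants" and makes no distinction between groups.

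Participants defines the control group by number and matching variables: "30 healthy control participants (matched according to age, gender and educational level) will be recruited". It defines the single-disorder groups by label: "30 alcohol dependent only and 30 depressed only patients will be included for T1 assessment".

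Primary outcome names activation and connectivity in the reward system and the default mode network (DMN). The Background section on the DMN reports, from the study group's own earlier work, that "increased DMN connectivity in remitted depressed patients is associated with sadder mood, more rumination in daily life", and also with rumination and depression scores six months later.

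**The concern.** A healthy control group serves as the never-ill reference for both disorders. Under the stated window it need only be free of Axis I disorder for the last year. A person with major depression that ended 13 months ago meets the criterion, and so does a person whose alcohol dependence ended then.

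In many trials that would be an ordinary choice. Here the protocol's own rationale sits awkwardly with it: part of the primary outcome is a measure that the protocol describes as tracking mood, rumination and later course in people whose depression has remitted. If remitted people also differ on that measure from people who were never ill, every patient–control contrast at T1 would be made against a mixed reference. Those contrasts feed the first sub-objective under Aim, which is to separate signatures shared by the two disorders from signatures specific to their comorbidity.

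**Working it through.** **1. Does another section close the gap for controls?**

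| Place | What it fixes | Bars remitted illness in controls? |
|---|---|---|
| Eligibility, Axis I criterion | 12 months, all participants | No |
| Eligibility, medication | antidepressants permitted, no group limit | No; maintenance treatment is not a bar either |
| Participants | 30 controls; age, gender, education | No |
| Sample recruitment | telephone screening, content not shown | Not stated |
| Table 1 | diagnostic interview at T0 | Could record it; no rule stated |

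No section does so.

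**2. Does the window also decide entry to the single-disorder groups?** No. The bracket takes patients' alcohol and depressive symptoms out of this exclusion whatever the period. What separates the alcohol-dependent group from the depressed group is the word *only* in Participants together with the DSM-5 diagnosis. Neither place says whether *only* means current or lifetime.

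**3. What does the DMN section establish?** It reports associations within remitted patients. Bias in a control group needs a difference between remitted and never-ill people, and the section gives none. It offers nothing on remitted alcohol dependence.

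**4. The nearest stated figure.** The criterion has no figure of its own. Sample size states 80% power for 30 per group at d = 1, Bonferroni corrected, with a 200-voxel region. A two-sided two-sample t-test (noncentral t) with 30 v 30 gives 0.97 at alpha = .05 and 0.50 at .05/200 = .00025. The 80% is not reproduced at either level. That is a separate matter, and nothing below rests on it.

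**5. Illustration of size.** Let a share q of controls have remitted illness, and let each carry a shift s, in SD units, in the direction of the patient effect. With a true difference of 1:

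- observed difference = 1 − q·s
- control variance = 1 + q(1 − q)s²
- effective d = (1 − q·s) / √[(1 + control variance)/2]

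Neither q nor s is in the documents; both are assumptions. For q = 5–15% and s = 0.5–1 the shift q·s runs from 0.05 × 0.5 = 0.025 to 0.15 × 1 = 0.15 SD. For q = 10% and s = 0.5, effective d = 0.95 / √[(1 + 1.0225)/2] = 0.945. Power for 30 v 30, two-sided:

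| q (of 30) | s | effective d | alpha .05 | alpha .05/200 |
|---|---|---|---|---|
| 0 | – | 1.000 | 0.97 | 0.50 |
| 10% (3) | 0.5 | 0.945 | 0.95 | 0.42 |
| 20% (6) | 0.5 | 0.891 | 0.92 | 0.34 |
| 30% (9) | 0.5 | 0.839 | 0.89 | 0.28 |
| 10% (3) | 1 | 0.880 | 0.92 | 0.33 |
| 20% (6) | 1 | 0.770 | 0.83 | 0.20 |
| 30% (9) | 1 | 0.666 | 0.72 | 0.11 |

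The 20% and 30% rows lie beyond the 5–15% range and serve as outer bounds.

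**6. Direction.** The table assumes s > 0. If s = 0 there is no bias. If s is negative the contrast widens: q = 10% and s = −0.5 gives 1 + 0.05 = 1.05. The Background does not settle the sign. Depression is described with reduced accumbens activity. Alcohol dependence is described with reduced ventral striatal activation in some studies and increased activation in the group's own, and its DMN findings are given as increased, mixed or reduced. Past alcohol dependence among controls could therefore shrink or widen a contrast with depressed patients.

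**The case against.** The strongest reply is that a 12-month window is a defensible choice. Participants free of any lifetime history represent the population less well and are harder to recruit. The article is also condensed: the telephone screening may already ask about lifetime history, and sensitivity analyses normally belong in the analysis plan. The DMN passage supplies no contrast with never-ill people, and every magnitude above is assumed.

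Much of this stands. It rules out any signed or sized claim of bias, and it leaves lifetime exclusion in the single-disorder groups as a genuine trade-off. It does not answer the point about controls, because the 12-month period is a criterion the article states, not a detail it leaves out.

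A reader might go further and infer that the window also puts people with past comorbidity into the wrong single-disorder group. On that reading the comorbid versus alcohol-only difference shrinks and a false alcohol effect appears against controls, with the Background's odds ratio of 4.7 making the misfiling uneven. The documents do not support this. The exemption for patients means the window is not what admits them. The odds ratio is given without a time frame, so it says nothing about depression that ended more than a year ago. The opposing findings cited in the Background leave the sign of any shift open.

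**Conclusion.** The point holds for the 30 healthy controls: as written, depression or alcohol dependence that remitted more than 12 months ago does not exclude them, and part of the primary outcome is a measure the protocol regards as informative in remitted depression. Whether this biases the T1 contrasts, by how much and in which direction, cannot be determined from the documents. The 0.025–0.15 SD shift is only what the assumed shares and retained effects imply if the shift runs in the patients' direction. For the single-disorder groups the weakness is an undefined label, not the window. The randomised comparison of behavioural activation with mindfulness training uses comorbid patients only and is untouched. This is an inexpensive improvement to the cross-sectional part of the study, not a flaw that invalidates it.

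**What to change.** 1. In Eligibility, require that healthy controls have no lifetime depressive disorder and no lifetime alcohol use disorder. Keep the 12-month window for other Axis I disorders.
2. Code lifetime history of both disorders for every participant from the structured diagnostic interview that Table 1 already schedules at T0. Table 1 names the DSM-IV interview while group diagnosis follows DSM-5, so state which categories count as a history.
3. Repeat the comorbid versus alcohol-only and comorbid versus depressed-only contrasts without single-disorder patients who have a history of the other disorder. This keeps entry to those groups open and shows whether the result depends on such patients.

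The cost is a change of wording, lifetime coding in an interview already planned, slightly slower recruitment of 30 controls, and one extra sensitivity analysis.
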